## Abstract

**Background:**

The prevention of overweight and obesity during infancy is a highly relevant public health topic given the significant impact of childhood obesity on acute and chronic diseases, general health, and well-being in later stages of life. Apart from the family setting, daycare facilities (DFs) represent a key setting for health promotion among children under the age of six years. “JolinchenKids – Fit and Healthy in Daycare” is a multi-component program promoting physical activity (PA), healthy eating, and mental well-being in 3- to 6-year-old preschoolers at DFs, originally designed by the German health insurance AOK. To evaluate program effectiveness, a cluster-controlled trial involving 68 DFs is currently conducted. The objective of this article is to describe the background, study design, and aims of this trial.

**Methods/design:**

Sixty-eight DFs across Germany will be recruited to take part in the study, half of them serving as intervention DFs and half of them as delayed intervention control DFs (which receive the program upon completion of the study). At each DF, height, weight, and body composition, as well as motor skills, will be assessed in twenty 3- to 6-year-old children. Children’s eating and PA habits, and mental well-being will be assessed via parental questionnaires. A subsample of children (i.e., at 24 DFs which are randomly selected within a geographic region) will be asked to wear accelerometers at their wrists to objectively measure PA over the course of seven days. To compare changes in body composition, motor skills, eating and PA habits, and mental well-being of children at intervention DFs with those observed among children at delayed intervention control DFs over one year, all measurements will take place at baseline and twelve months after the launch of the program at all DFs.

**Discussion:**

This study investigates the influence of a health promotion program in the daycare setting on various outcomes, including body composition and objectively measured PA, in a nationwide sample of 3- to 6-year-old preschoolers. This study will provide evidence regarding the effectiveness of a multi-component program for health promotion in this setting and may provide insights into new strategies for preventing obesity in early life.

**Trial registration:**

German Clinical Trials Register DRKS00011065 (Date of registration 16–09-2016).

## Background

Data from the German Health Interview and Examination Survey for Children and Adolescents (KiGGS) indicate that one in eight children under the age of six is either overweight or obese in Germany [1]. Childhood overweight and obesity is accompanied by multiple negative health consequences in the short and long term [2–6]. There is also clear evidence that excessive weight gain in the first years of life increases the risk for obesity and chronic diseases, such as coronary heart disease, later in life [7–9]. In fact, obese preschool-aged children are five times more likely to be overweight during adolescence and have a four times increased risk to be obese in adulthood when compared to normal weight children [10]. Efforts to date have failed to halt the rise in childhood obesity. The implementation of comprehensive programs that promote the intake of healthy foods and physical activity (PA) and aim to reduce sedentary behavior in children and adolescents is therefore strongly recommended [11].

Unhealthy eating and PA habits which clearly contribute to the etiology and progression of obesity, are, to a great extent, learned during the first years of life and tend to persist into adulthood [12, 13]. Therefore, this period in life represents a powerful opportunity for impacting energy balance-related behaviors. In Germany, to date, 50% of children under the age of six years do not meet the current PA recommendation for their age group [14] and only one fifth of 3- to 6-year-old children consume the recommended five or more portions of fruits and vegetables per day [15]. To date, even well-designed studies examining the effects of interventions targeting these two behaviors to prevent or reduce childhood overweight and/or obesity yielded no, inconsistent, or only weak effects [16]. To conclude, there is still a lack of studies demonstrating substantial or clinically meaningful changes in body composition and eating and PA habits under real-life conditions in this population.

Daycare facilities (DFs) are a key setting for early health promotion. Findings of a recent systematic review suggest that there is a strong potential to shape health-relevant attitudes and behaviors in the daycare setting [17] and some research indicates that parents may easily be involved in daycare-based interventions [18]. Furthermore, many children spend the majority of their waking hours in this setting. For example, in Germany, more than 3.5 million children are taken care of in DFs, 27% for more than seven hours every day [19].

“JolinchenKids – Fit and Healthy in Daycare” is a multi-component program, originally designed by the German health insurance AOK, aimed at modifying the daycare environment and individual health behavior among children. Both, daycare staff and parents, are involved in the implementation of the program. Because data gathered in qualitative research in the school setting suggest that administrators and teachers feel under-qualified to deliver nutritional information [20], training in delivering the intervention and intervention messages is offered to daycare staff by external specialists in the fields of nutrition, PA, and mental well-being over a three-year period as part of the program.

In the following sections, the research design and methods of a cluster-controlled trial (CCT) evaluating the impact of “JolinchenKids – Fit and Healthy in Daycare” at 68 daycare facilities are described. The main objective of this trial, funded by the German health insurance AOK, is to evaluate program-associated changes in body composition, behavioral and psychological outcomes in a nationwide sample of preschoolers comparing children enrolled at 34 intervention DFs with those enrolled at 34 delayed intervention control DFs.

## Methods

### Study aims

The primary aim of the study is to evaluate whether children participating in the program at the 34 intervention DFs demonstrate greater changes in body composition and behavioral and psychological outcomes compared to those enrolled at the 34 delayed intervention control DFs. Secondary aims of the study are:(I)To evaluate whether the daycare environment at DFs is modified as part of the program to support changes in individual health behavior of children;(II)To examine whether DF staff make lifestyle changes recommended to them as part of the program;(III)To adapt future program implementation based on results gathered in focus groups with DF staff, parents, and preschool-children on factors facilitating or hindering implementation.

### Study design

Due to the risk of cross-contamination of intervention effects, it was not feasible to allocate children to the intervention or non-intervention conditions at individual DFs [21]. Randomization of DFs to intervention vs. control conditions was also not possible (see below for reasons and recruitment of DFs in the study). Therefore, this study was planned as a CCT with a non-random allocation procedure. CCT designs are used not only to evaluate group interventions but also individual interventions where group level effects are relevant [22]. Therefore, clusters in this study constitute the kindergarten groups of the individual DFs (one group per DF). These clusters will be allocated to intervention and control groups and outcomes will be measured among individuals within those clusters.

### Inclusion criteria

DFs have to fulfil the following criteria to be included in the study: (1) > 14 children aged three to five years are currently taken care of at the individual DF; (2) the DF is organized in groups; (3) there is sufficient room for conducting the tests for assessing motor skills; and (4) the head of the DF agrees to participate in the study and signs a letter of consent. DFs will be excluded if they do not meet these criteria.

### Participants and procedures

Ethical approval for the study was obtained from the Medical Association in Bremen (HR/RE – 522). For the recruitment of 68 DFs, the following recruitment strategy will be employed. The health insurance AOK determines when DFs start with the implementation of the intervention. Therefore, it is not feasible to randomly allocate DFs to either intervention or delayed intervention control conditions. To facilitate the recruitment process, the AOK will provide two lists, each of them containing addresses of possible intervention or delayed intervention control DFs from various German federal states. In each federal state, DFs from both lists will be randomly selected and invited to participate in the study via mail. Heads of DFs will receive general information on the study and a short questionnaire. In this questionnaire, the following data will be assessed to later match intervention and delayed intervention control DFs: Estimates of the percentage of parents with lower levels of education and income at the DF, estimated percentage of parents with migration background, and other indicators for the distribution of socio-economic status among parents (i.e., the percentage of parents receiving subsidies from the government for payment of DF fees, percentage of single parents). In addition, this questionnaire will include questions that help the research staff organize baseline and follow-up assessments (e.g., number of children between the ages of three and five years at the DF). The heads of DFs of the DFs fulfilling the inclusion criteria described above will be asked for a written consent to participate in the study and will subsequently be contacted via telephone to arrange the dates for baseline and follow-up assessments. Heads of DFs will subsequently be in charge of the recruitment of the children at their facility. We expect that the heads of DFs will be familiar with all parents which may facilitate recruitment of children. Parents and their children will then be recruited to the study via written invitations which are provided to the heads of DFs by the research institute and forwarded to the parents by them. In addition, a telephone hotline will be made available to parents to answer questions arising during recruitment. A maximum of 25 children per DF will be invited to participate in the study.

Parents will be informed that they and their children can withdraw from the study at any time. To participate in the study, children have to agree to participate and parents will be asked to give their written consent and to complete the parental baseline and follow-up questionnaires. Heads of DFs or other DF staff assigned to recruitment will collect the completed written consent forms and questionnaires from the parents (at baseline and follow-up) and will send them to the research institute in the mail.

### Sample size

Sample size was calculated with regard to the two primary outcomes diet and PA. Based on a prevalence of fruit consumption reported in a previous study conducted at 64 German DFs including 2.658 preschoolers which reported rates of fruit consumption of 66.7% in the intervention group and 56% in the control group [23], we assumed a difference in the change in diet from baseline to 12-months follow-up of 8% between intervention and control group considering an estimated intracluster correlation coefficient (ICC) of 0.02, 90% power, and α = 0.05 (two-sided). Based on this, we estimated that a total of 1.020 children at 68 DFs would be required for our study. With regard to more conservative estimates for the ICC, this sample size will provide more than 80% power to detect changes of 8% in fruit consumption. We assumed a 25% loss to follow-up twelve months post-baseline. Therefore, we aim to reach 1360 children, in total, at baseline, twenty children at each of the 68 participating DFs. According to De Bock et al. [24], little is known about the extent to which PA-related outcomes in preschool children are inter-correlated. Therefore, our sample size calculation for detecting changes in objectively measured PA is based on the conservative assumption of an ICC of 0.1. To detect a difference of 0.5 standard deviations between intervention and control groups, we assumed a standard deviation of 38 counts per 15 s [24], a power of 90%, and α = 0.05 (two-sided), and estimated that a total of 360 children at 24 DFs will be necessary for our study. We increased our recruitment goal to 20 children per DF (240 per arm) to account for a 25% loss to follow-up. All power calculations were carried out in PASS [25], using tests for two proportions in a cluster-randomized design function.

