### Analysis strategy

#### Quantitative analysis

To evaluate intervention effectiveness, changes in body composition, health behaviors, and psychological outcomes from pre- to post-test among children at intervention DFs will be compared to those observed in children enrolled at delayed intervention control DFs. In addition to descriptive data analyses, quantitative analyses will be performed involving simple two-sample t-tests, as well as mixed effects regression models. Such regression models account for the clustered structure of the data, allow for controlling of baseline differences between the groups and for considering potential confounders, such as age, gender, or parents’ educational attainment, simultaneously. All statistical analyses will be carried out using SAS 9.3 software (SAS Institute Inc., Cary, NC) [32].

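### The 90% power is claimed for a difference in change, but the printed sample-size inputs contain no baseline-to-follow-up correlation and so do not support it for that comparison

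*Protocol article*

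**What the plan says.** In the Protocol article, Sample size, the diet calculation starts from an earlier study with "rates of fruit consumption of 66.7% in the intervention group and 56% in the control group". It then fixes the target: "we assumed a difference in the change in diet from baseline to 12-months follow-up of 8% between intervention and control group". The other diet inputs are an "estimated intracluster correlation coefficient (ICC) of 0.02", 90% power and a two-sided α of 0.05, leading to "a total of 1.020 children at 68 DFs would be required for our study".

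The PA calculation in the same section is introduced as one for detecting changes. It uses a difference of 0.5 SD, an ICC of 0.1, 90% power and a two-sided α of 0.05, and arrives at 360 children at 24 facilities. On the spread it says "we assumed a standard deviation of 38 counts per 15 s". The section adds that all calculations were done in PASS, "using tests for two proportions in a cluster-randomized design function".

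Under Quantitative analysis, the arms are compared on "changes in body composition, health behaviors, and psychological outcomes from pre- to post-test". Two tools are listed: simple two-sample t-tests, and mixed-effects regression models that account for clustering and can control for baseline differences.

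**The concern.** A test of two proportions takes one proportion per arm. A change score has a different variance from a single measurement: if both occasions have the same variance, the variance of the change is 2(1 − r) times that of one occasion. Power for a comparison of changes therefore cannot be stated without r or an SD of the change. The section gives neither, and it does not print the two proportions behind the 8%.

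The plan also leaves open which analysis the 90% refers to. An unadjusted comparison of changes loses precision against a single-time-point comparison when r is below 0.5, whereas a baseline-adjusted model does not. A null result from the unadjusted comparison could then be read as good evidence of no effect on the strength of a power figure that does not belong to it.

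**Working it through.** **Inputs from Sample size.** Diet: 1,020 children at 68 facilities after loss, so 15 per facility and 510 per arm; ICC 0.02; difference 8%, read as percentage points. PA: 360 children at 24 facilities, so 15 per facility and 180 per arm; ICC 0.1; difference 0.5 SD.

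**Assumptions of this check.** The inputs are single-time-point values. The diet proportions are 56% vs 64%, or 66.7% vs 74.7% (8 points added to each printed source rate). The planning ICC also applies to changes and to adjusted values. The value of r is not in the document, so a range is used.

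**Step 1: the plan's own figure, at one time point.** Design effect = 1 + (15 − 1) × ICC.
- Diet: 1 + 14 × 0.02 = 1.28; effective n per arm = 510/1.28 = 398.4.
  - 56% vs 64%: SE = √[(0.56×0.44 + 0.64×0.36)/398.4] = 0.0346; 0.08/0.0346 = 2.31; power = Φ(2.31 − 1.96) ≈ 64%.
  - 66.7% vs 74.7%: SE = √[(0.667×0.333 + 0.747×0.253)/398.4] = 0.0321; ratio 2.49; power ≈ 70%.
- PA: 1 + 14 × 0.1 = 2.4; effective n per arm = 180/2.4 = 75; SE = √(2/75) = 0.163 SD; 0.5/0.163 = 3.06; power ≈ 86% (normal), 83% (t on 22 df).

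The printed 90% is not reproduced at a single time point. That is a separate matter, but it sets the starting level for what follows.

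**Step 2: effect of r.** Divide the ratios above by √[2(1 − r)] for unadjusted change scores, or by √(1 − r²) for follow-up adjusted for baseline. Ranges run from a t reference (22 df for PA, 66 df for diet) to the normal one and, for diet, over both pairs of proportions.

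| r | PA, change | PA, adjusted | Diet, change | Diet, adjusted |
|---|---|---|---|---|
| 0.3 | 70–74% | 87–89% | 49–56% | 67–74% |
| 0.5 | 83–86% | 92–94% | 63–70% | 75–82% |
| 0.7 | 97–98% | 98–99% | 84–90% | 89–94% |

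Example, PA at r = 0.3: change 3.06/√1.4 = 2.59, Φ(2.59 − 1.96) ≈ 74%; adjusted 3.06/√0.91 = 3.21, Φ(3.21 − 1.96) ≈ 89%.

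**Step 3: r needed for 90%.** The ratio must reach 1.96 + 1.28 = 3.24, so the variance factor may be at most (ratio/3.24)².
- PA: (3.06/3.24)² = 0.89. Change: r = 1 − 0.89/2 ≈ 0.55 (about 0.59 with t on 22 df). Adjusted: r = √(1 − 0.89) ≈ 0.33 (about 0.43 with t).
- Diet, 56% vs 64%: (2.31/3.24)² = 0.51. Change: r ≈ 0.75. Adjusted: r ≈ 0.70.
- Diet, 66.7% vs 74.7%: (2.49/3.24)² = 0.59. Change: r ≈ 0.70. Adjusted: r ≈ 0.64.

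**Step 4: the part due to this point alone.** At r = 0.3, moving from one time point to unadjusted change costs about 13 to 14 percentage points of power for both outcomes (PA 86% to 74%, or 83% to 70% with t; diet 64% to 50%, or 70% to 56%). The rest of the gap to 90% was already there in Step 1.

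**The case against.** **The inputs may already refer to change.** The two proportions behind the 8% are not printed. If they were proportions of children who change, a two-proportion test would suit the target; 10% vs 18%, for instance (an assumption, not in the document), would give about 90% power with 1,020 children. Likewise, 38 counts could be the SD of a change; its source is not at hand. This stands: sizing for a single time point is an inference, and the figures above are conditional on it. It does not rescue the statement as printed, because the only rates shown are 56% and 66.7% and nothing identifies 38 as a change SD.

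**The plan already provides the remedy.** Mixed models that can control for baseline are listed, and with the baseline value as covariate the variance factor 1 − r² never exceeds 1. This stands too. The extra loss below r = 0.5 concerns only the unadjusted comparison. But the plan also lists simple t-tests and does not say which analysis the 90% describes.

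**A condensed article may leave r to the full protocol.** That would hold if the article only named a sample size. It prints the effect, SD, ICC, method and power, and ties the diet effect to a change.

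**Stronger readings.** A reader might infer that the plan delivers its 90% only at r = 0.5 exactly. It does not: r = 0.5 merely makes the two variances equal, the printed inputs give 83 to 86% (PA) and 63 to 70% (diet) there, and power keeps rising with r. A reader might also infer that the comparison of changes should be demoted to a sensitivity analysis. With non-random allocation (Study design), change scores and baseline adjustment rest on different assumptions, and the document gives no ground for calling one plainly better.

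**Conclusion.** The point holds in a limited form: the stated 90% is unsupported for the comparison of changes, because the printed method carries neither a correlation nor an identified SD of change. The documents do not show that the trial was sized for the wrong comparison, since the inputs are not labelled either way.

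Under the single-time-point reading and an unchanged ICC, the size depends on r and on the analysis. With r near 0.3, an unadjusted comparison of changes falls well short of 90% for both outcomes, while the baseline-adjusted model comes close for PA and remains well short for diet. With r near 0.7, PA exceeds 90% under either analysis and diet comes close to it or passes it. The diet shortfall under the adjusted model comes from the printed inputs themselves, not from the use of change. If the ICC of changes or adjusted values differs from the planning value, all these figures shift.

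**What to change.** In Sample size:
- Restate the power, or the detectable difference, for the analysis that will be run.
- Say whether 38 counts is the SD of a level or of a change.
- Print the two proportions behind the 8% and say whether they are levels or rates of change.
- Show power over an assumed range of the baseline-to-follow-up correlation, such as 0.3 to 0.7.

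Tie the restated figure to the mixed model that accounts for clustering and controls for baseline, as already described under Quantitative analysis, and not to the simple two-sample t-test. The comparison of changes can keep its place in the plan.

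The cost is one recalculation and a few sentences, with no extra children or measurements. The downside is that the stated power may become less favourable.

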In a subsample of children at 24 DFs (12 intervention and 12 delayed intervention control DFs, ca. *n* = 360), PA will be assessed objectively using wrist-worn triaxial accelerometer watches (GENEActives, produced by ActivInsights Ltd.) for seven consecutive days at baseline and follow-up. The GENEActives provide raw accelerometry data in three axes (activity counts measured at 100 Hz) and measure surface skin temperature. They were chosen for the study because they are light-weight and waterproof and can be worn at the wrists meaning that they are more comfortable for continuous 24 h use among small children compared to the hip-worn version of the activity monitor. Compliance among small children has been shown to be greater when using wrist-worn accelerometers compared to hip-worn devices [27]. Reliability and validity of GENEActive measurements in children have been widely demonstrated for children above the age of eight years [28, 29]. The validity of this activity monitor for preschool-aged children is currently examined in another study [30]. Study nurses will mount the device on the left wrist because the majority of children is expected to be right-handed and it is recommended to use the non-dominant hand for measurement because energy prediction is more precise this way [29]. Handedness will also be assessed via parental questionnaire and controlled for in later statistical analysis. Parents of children of this subsample receive instructions regarding the recommended wear time and properties of the device, and a paper-and-pencil diary to report wear and non-wear times and to document reasons for not wearing the device.

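### The accelerometer sample size of 360 analysed children at 24 facilities gives about 83–86% power for 0.5 SD at ICC 0.1, not the stated 90%, and the software procedure named cannot have sized a mean

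*Protocol article*

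**What the plan says.** The Sample size section names diet and PA as the two primary outcomes and sizes each separately. For accelerometer-measured PA it takes an ICC of 0.1, described as conservative, and sets the target as follows: "To detect a difference of 0.5 standard deviations between intervention and control groups", where "we assumed a standard deviation of 38 counts per 15 s". With 90% power and a two-sided alpha of 0.05, the authors "estimated that a total of 360 children at 24 DFs will be necessary for our study". The next sentence allows for attrition: "We increased our recruitment goal to 20 children per DF (240 per arm) to account for a 25% loss to follow-up". The section closes by saying that all power calculations were run in PASS, "using tests for two proportions in a cluster-randomized design function".

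The Assessments section places the devices "In a subsample of children at 24 DFs (12 intervention and 12 delayed intervention control DFs" and adds, in the same parenthesis, an approximate n of 360. Measurement is for seven days at baseline and again at follow-up.

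**The concern.** Every input needed to reproduce the PA figure is printed, so it can be checked directly, and it does not come out at 90%. The procedure named for the calculation takes two proportions, whereas this outcome is a mean with an SD in counts per 15 s, so a reader who follows the text cannot regenerate 360. The number of children in the accelerometer subsample is also unclear: the Sample size section recruits 480 to retain 360, while the Assessments section mentions only about 360.

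PA is one of the two outcomes on which the trial was sized. A null accelerometer result would be read against a claimed 90% chance of detecting half a standard deviation. If the real figure is lower, that reading is too confident. If the smaller number were taken as the number of devices to fit, power would fall further.

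**Working it through.** **Inputs**

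| Input | Value | Source |
|---|---|---|
| Difference | 0.5 SD (19 counts at SD 38) | Sample size |
| ICC | 0.1 | Sample size |
| Alpha | 0.05, two-sided | Sample size |
| Target power | 90% | Sample size |
| Analysed children, DFs | 360 at 24, so 15 per DF | Sample size |
| DFs per arm | 12, so 180 analysed per arm | Assessments |
| Recruited | 20 per DF, 240 per arm, 480 in total | Sample size |

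That 360 is the analysed number follows from the attrition step: 480 × 0.75 = 360. This part of the arithmetic is correct.

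**Attempt to reproduce the 90%**

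- Design effect = 1 + (15 − 1) × 0.1 = 2.4.
- Effective n per arm = 180 / 2.4 = 75.
- Standard error in SD units = √(2/75) = 0.1633.
- Noncentrality = 0.5 / 0.1633 = 3.06.
- Normal approximation: Φ(3.06 − 1.96) = 86.5%.
- Noncentral t with 358 df (individuals): 86.3%.
- Noncentral t with 22 df (24 clusters − 2): 83.3%.

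The stated 90% is not reproduced by any of the three.

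**What 90% would need on the stated assumptions (normal approximation unless noted)**

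- Per arm: 2 × (1.960 + 1.282)² / 0.5² × 2.4 ≈ 202, or about 404 analysed in total against 360.
- Whole DFs of 15 analysed children: 14 per arm (normal, 91.1%) or 15 per arm (t, 91.1%).
- Detectable difference with the present design: 3.24 × 0.1633 = 0.53 SD, or 20.1 counts. With t on 22 df the required noncentrality is 3.39, giving 3.39 × 0.1633 = 0.55 SD.

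**Variants that come close to 90%**

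| Variant | Normal | t, 22 df |
|---|---|---|
| 20 analysed per DF (no loss; design effect 2.9, effective n 82.8) | 89.6% | 86.7% |
| Difference of 20 counts instead of 19, 15 per DF | 89.7% | 86.9% |
| One-sided alpha 0.05, 15 per DF | 92.2% | 90.7% |

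None of these matches the printed inputs. The first two are equally close by the normal approximation, so the result does not point to one particular slip.

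**Baseline adjustment**

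If adjusting for baseline reduces the variance by the factor 1 − r², with the same r between and within DFs (an assumption), the noncentrality becomes 3.06 / √(1 − r²).

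- Normal: 1 − r² = (3.062 / 3.242)² = 0.892, so r ≈ 0.33 is needed.
- t on 22 df: 1 − r² = (3.062 / 3.393)² = 0.814, so r ≈ 0.43 is needed.

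The article states no such correlation.

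**If only 360 were fitted and 25% lost**

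- Analysed: 360 × 0.75 = 270, or 135 per arm and 11.25 per DF.
- Design effect = 1 + 10.25 × 0.1 = 2.025; effective n = 135 / 2.025 = 66.7; noncentrality = 2.89.
- Power: 82.3% (normal) or 78.8% (t, 22 df).

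**The case against.** Four points can fairly be made for the plan.

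- **The shortfall is modest.** By the normal approximation it is 3.5 points, or about one count per 15 s in the detectable difference. This stands, and it limits how much the error matters. It does not make the printed figure correct.
- **The analysis may have more power than the calculation.** The Quantitative analysis section plans mixed models that control for baseline differences, alongside simple t-tests. A moderate correlation of 0.33 to 0.43 would bring 360 children to 90%. This also stands, and it is why a single figure of 83% should not be imposed. But the sample-size text neither credits adjustment nor gives a correlation, so its 90% does not follow from its own inputs.
- **The source of the error is unknown.** A reader might infer that the recruited cluster size of 20 was entered and that the attrition allowance was thereby spent. The document does not support that: a difference rounded to 20 counts does equally well with 15 per DF and the allowance intact, and the software entries are not shown.
- **The approximate 360 in Assessments may mean completers.** A reader might infer a plan to fit only 360 devices at baseline. The text does not say so. The figure equals the analysed number, and the parenthesis describes children measured at both time points. It is an ambiguity, not a demonstrated contradiction, and the 79–82% figure applies only under the less favourable reading.

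A reader might also see a units problem, because the SD is in counts per 15 s while the device delivers raw 100 Hz data. The Assessments section itself calls the device output activity counts, and the power depends only on the effect in SD units, so nothing here turns on it.

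**Conclusion.** The PA power statement is wrong as written. On the printed inputs, 360 analysed children at 24 DFs give about 86% power (normal approximation) or 83% (t on 22 df) for 0.5 SD, which is 3.5 to 6.7 points below the stated 90%. This assumes equal cluster sizes of 15, 12 DFs per arm, the usual design effect and no baseline adjustment. How 360 was obtained cannot be determined from the document.

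The sentence on software cannot hold for the PA outcome, because a two-proportions procedure has no place for a mean and an SD. The approximate 360 in Assessments needs clarifying so that it cannot be read as the number to fit at baseline.

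**What to change.** Three changes to the text:

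1. In Sample size, state that 24 DFs with 15 analysed children each give about 83–86% power for 0.5 SD at ICC 0.1 before baseline adjustment, with 90% corresponding to 0.53–0.55 SD. Alternatively, keep 90% and state and justify the baseline–follow-up correlation it relies on (about 0.33 by the normal approximation, 0.43 by t on 22 df).
2. Limit the two-proportions procedure to the diet calculation and cite a two-means cluster procedure for PA.
3. In Assessments, say that about 480 children are fitted with devices at baseline and about 360 are expected to have both measurements, in line with the recruitment goal.

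The recruitment goal is already 480, so no extra children or DFs are needed. The cost is a slightly less favourable stated power.
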